# The CombinADO study to assess the impact of a combination intervention strategy on viral suppression, antiretroviral therapy adherence, and retention in HIV care among adolescents and young people living with HIV: protocol for a cluster-randomized controlled trial

**DOI:** 10.1186/s13063-021-05943-w

**Published:** 2021-12-27

**Keywords:** Adolescent, Youth, HIV, Mozambique, Cluster-randomized controlled trial, Multi-component intervention, Viral suppression, ART adherence, Retention, Implementation

## Abstract

**Background:**

Adolescents and youth living with HIV (AYAHIV) have worse HIV outcomes than other age groups, particularly in sub-Saharan Africa (SSA). AYAHIV in SSA face formidable health system, interpersonal- and individual-level barriers to retention in HIV care, uptake of ART, and achievement of viral suppression (VS), underscoring an urgent need for multi-component interventions to address these challenges. This cluster-randomized control trial (cRCT) aims to evaluate the effectiveness and monitor implementation of a community-informed multi-component intervention (“CombinADO strategy”) addressing individual-, facility-, and community-level factors to improve health outcomes for AYAHIV.

**Methods:**

This trial will be conducted in 12 clinics in Nampula Province, Northern Mozambique. All clinics will implement an optimized standard of care (control) including (1) billboards/posters and radio shows, (2) healthcare worker (HCW) training, (3) one-stop adolescent and youth-friendly services, (4) information/motivation walls, (5) pill containers, and (6) tools to be used by HCW during clinical visits. The CombinADO strategy (intervention) will be superadded to control conditions at 6 randomly selected clinics. It will include five additional components: (1) peer support, (2) informational/motivational video, (3) support groups for AYAHIV caregivers, (4) AYAHIV support groups, and (5) mental health screening and linkage to adolescent-focused mental health support. The study conditions will be in place for 12 months; all AYAHIV (ages 10–24 years, on ART) seeking care in the participating sites will be exposed to either the control or intervention condition based on the clinic they attend. The primary outcome is VS (viral load < 50 copies/mL) at 12 months among AYAHIV attending participating clinics. Secondary outcomes include ART adherence (self-reported and TDF levels) and retention in care (engagement in the preceding 90 days). Uptake, feasibility, acceptability, and fidelity of the CombinADO strategy during implementation will be measured. Trial outcomes will be assessed in AYAHIV, caregivers, healthcare workers, and key informants. Statistical analyses will be conducted and reported in line with CONSORT guidelines for cRCTs.

**Discussion:**

The CombinADO study will provide evidence on effectiveness and inform implementation of a novel community-informed multi-component intervention to improve retention, adherence, and VS among AYAHIV. If found effective, results will strengthen the rationale for scale up in SSA.

**Trial registration:**

ClinicalTrials.gov NCT04930367. Registered on 18 June 2021

**Supplementary Information:**

The online version contains supplementary material available at 10.1186/s13063-021-05943-w.

## Background

HIV burden among adolescents and young adults (aged 10–24) worldwide is substantial, with an estimated 1.7 million adolescents aged 10–19 years living with HIV in 2019 and 460,000 adolescents and youth newly infected in the same year [1]. An estimated 85% of all adolescents and young people living with HIV (AYAHIV) reside in sub-Sharan Africa [SSA] [2]. This is concerning given that SSA has a young population, with 30–35% of the total population between 10 and 24 years of age [1]. While increased availability and access to antiretroviral therapy (ART) have significantly reduced pediatric mortality, healthcare workers (HCWs) face challenges in meeting the complex needs of the large number of surviving AYAHIV who must learn to manage HIV, a chronic, highly stigmatized, and transmittable illness. Furthermore, adolescents and young adults newly acquiring HIV in these developmental stages experience overlapping but distinct and equally complex needs that require tailored services.

AYAHIV in SSA face formidable health system, interpersonal- and individual-level barriers to retention in HIV care, uptake of ART, and achievement of viral suppression (VS) and worse outcomes compared to other age groups within HIV programs have been identified [3]. Results from the Population HIV Impact Assessments (PHIA) in four SSA countries, Zambia, Zimbabwe, Malawi, and Eswatini, demonstrated lower rates of HIV testing, ART uptake, and VS among 15–19-year-olds compared with adults [4]. Previous studies conducted in SSA have identified multiple factors impacting treatment outcomes in AYAHIV, many in common with adult populations but compounded by the challenges of adolescence and early adulthood, including psychosocial factors and lack of social support, as well as factors relating to health systems such as mistrust of HCWs and concerns about stigma and discrimination, especially when accessing sexual and reproductive health (SRH) services [5–11]. Evidence from our formative survey among 213 AYAHIV ages 10–19 years surveyed in Nampula Province Mozambique showed a high proportion of participants with missed ART doses and high levels of viremia, and over two-thirds self-reported challenges with ART adherence [12–14].

There are few evidence-based interventions designed to promote increased retention in care, ART adherence, and VS among AYAHIV in low- to middle-income countries (LMIC). Peer support and support groups are the most widely used approaches, seen in Malawi with adolescent-centered differentiated service delivery (DSD), which integrates structured adolescent-focused groups, adherence counseling, and social activities into clinic visits which are aligned with school hours which has been associated with higher retention; and a peer-supported community-based DSD model in Zimbabwe that demonstrated significantly improved VS among AYAHIV [15, 16]. In addition, counseling and education (individual, family, group multidisciplinary with AYAHIV and/or caregivers) have been noted as modestly associated with improved adherence among AYAHIV [17].

Mozambique has the second-highest number of new HIV infections in Eastern and Southern Africa, high HIV burden among adolescents, and poor treatment coverage with progress towards the UNAIDS 95-95-95 targets for HIV epidemic control lagging behind other countries in the region [18]. HIV prevalence in Mozambique is 13.2%, with an estimated 1.8 million people living with HIV (PLHIV). More than 30% of the general population is aged between 10 and 24 years, and they face high rates of poverty and unemployment and poor access to education, all of which contribute to poor health outcomes [19]. Nationally, there are an estimated 143,000 AYAHIV, 10–19 years, only half of whom (54%) are currently on ART [20)]. Despite improving access to care and better outcomes for those initiated on ART, rates of VS remain low, especially among young men. Among AYAHIV ages 10–14, 15–19, and 20–24, VS among females is 64%, 72%, and 80%, respectively, and VS among males is 60%, 62%, and 75%, respectively [20–22]. Mozambique has a national package of adolescent and youth-friendly services (AYFS), including HIV prevention, care, and treatment, screening, and treatment for sexually transmitted infections (STIs), family planning, and intimate partner violence (IPV) services. However, in parts of Mozambique, AYFS have only been implemented in only a few health facilities [23]. These gaps underscore the need for developing a youth-focused multi-component combination intervention for AYAHIV in Mozambique.

Recognizing the paucity of evidence to inform the successful scale-up of quality services for children and adolescents living with HIV, WHO and CIPHER developed a global research agenda that emphasized the need for effective strategies to improve adherence, retention, SRH outcomes, and service delivery models to improve outcomes along the HIV continuum, including peer interventions and DSD models [24]. Furthermore, the National Institute of Child Health and Development (NICHD) requested research proposals to generate much needed scientific innovation to yield effective public health interventions for young people affected by HIV in resource-limited settings, the Prevention and Treatment through a Comprehensive Care Continuum for HIV-affected Adolescents in Resource-Constrained Settings (PATC^3^H) program. In collaboration with the Mozambique Ministry of Health (MISAU), researchers from ICAP at Columbia University were awarded a grant to develop and evaluate a complex, multi-component intervention to improve HIV related health outcomes of AYAHIV in Mozambique (CombinADO).

The CombinADO project is unique in its focus on shifting the paradigm of AYAHIV services from one of fear and secrecy to one of hope and inclusion. The formative work conducted during the initial phase of CombinADO has enhanced the evidence base with rich information regarding the needs of AYAHIV and best practices around AYAHIV engagement to help increase the adoption of interventions. Building on this, collaborations with a broad array of local stakeholders have led to the design and development of a multi-component intervention strategy that will be trialed in this study.

### Objectives

The primary objective is to evaluate the efficacy of the intervention (hereafter “*CombinADO strategy*”) on the rate of HIV VS among AYAHIV receiving HIV care at 12 health facilities in Nampula, Mozambique. The secondary objectives are (1) to examine the efficacy of the CombinADO strategy on the rate of retention in care among AYAHIV receiving HIV care at 12 health facilities in Nampula Mozambique; (2) to evaluate the efficacy of the CombinADO strategy on the rate of adherence to ART among AYAHIV receiving HIV care at 12 health facilities in Nampula Mozambique; (3) to assess the uptake, feasibility, and acceptability of the CombinADO strategy at 12 health facilities in Nampula Mozambique; and (4) to estimate the cost and incremental cost-effectiveness of the CombinADO strategy at 12 health facilities in Nampula, Mozambique.

## Methods and analysis

The study is conducted as part of the NICHD funded PATC^3^H consortium. The goal of PATC^3^H is to generate the needed scientific innovation that will yield effective public health interventions for adolescents (10–24 years) affected by HIV in Brazil and SSA [25]. This protocol was written following the Standard Protocol Items Recommendations for Interventional Trials (SPIRIT) guidelines (see Additional file 1: SPIRIT checklist).

### Study design

This is a cluster-randomized controlled trial (cRCT) designed to compare the effectiveness of the CombinADO strategy versus optimized standard of care (SOC) on VS, ART adherence, and retention in HIV care among AYAHIV ages 10–24 years attending participating health facilities. Clinics are the units of intervention allocation and randomization; however, trial outcomes will be assessed at the individual level among AYAHIV. An independent statistician will generate the clinic randomization schema. All AYAHIV seeking care will be exposed to either the control condition or intervention condition based on the facility attended. Health facility staff will implement the various intervention components at both the intervention and control sites as the standard of care for AYAHIV.

### Study setting

The study will be conducted in 12 study sites across Nampula Province, Northern Mozambique. The HIV prevalence among young people 15–24 years in this province is estimated at 4.1%, with only 16% of Nampula clinics currently offering youth-friendly services [23]. Clinics were eligible to be selected for participation based on location (within a 4-h drive from Nampula city), patient volume (at least 220 AYAHIV ages 10–24 currently active on ART), and one-stop-shop adolescent-friendly service model care. Out of 15 eligible clinics, 12 of these were randomly selected for participation by an independent biostatistician.

### Participants and recruitment

Eligible study participants include AYAHIV, AYAHIV caregivers, HCW, and key informants (KI). The eligibility criteria for the different groups are outlined in Table 1. The schedule for the various study activities for study participants is shown in Table 2.

**Table 1 Tab1:** Inclusion and exclusion criteria and the anticipated sample size of all the CombinADO study participants

Participant	Inclusion	Exclusion	Anticipated sample size
AYAHIV	HIV-positive, per medical records and confirmed by health facility staff Age 10–24 years Registered as a patient at the study site Aware of HIV+ status Provision of signed and dated informed consent form for adolescents aged 18 and above For adolescents aged 12–17, informed assent and parental informed consent to participate in the study For adolescents aged 10–11, parental consent to participate in the study Stated willingness to comply with all study procedures	Has an acute medical condition requiring immediate medical care	*N* = a minimum of 1200 and a maximum of 2400 for the post-intervention assessment *N* = a minimum of 360 and a maximum of 720 exit interviews
Caregivers	Age 18 years and older Attending a caregiver-specific support group Willingness to be audio-recorded	None	*N* = a minimum of 90 and a maximum of 120 semi-structured interviews
HCW	Age 18 years and older Involved in the provision, management, or oversight of adolescent-focused HIV services at the 12 specified study sites Willingness to be audio-recorded	None	*N* = a minimum of 70 and a maximum of up to 112 semi-structured interviews *N* = a minimum of 35 and a maximum of up to 50 costing questionnaires
KI	Age 18 years and older Involved in the provision, management, or oversight of adolescent-focused HIV services at the 12 specified study sites Willingness to be audio-recorded	None	*N* = a minimum of 32 and a maximum of 60 semi-structured interviews

**Table 2 Tab2:** Study assessment schedule for all the CombinADO participants

	Pre-intervention	Intervention implementation	Post-intervention

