#### AYAHIV

Up to 2400 AYAHIV (maximum of 200 AYAHIV per site) will be recruited to take part in a one-time post-intervention assessment at 12 months post-intervention implementation and up to 720 AYAHIV (maximum of 60 per site) in exit interviews during intervention implementation. Clinic staff will work with on-site study staff to review the daily schedule and list potentially eligible AYAHIV who have appointments. During the clinic visits at the 12 sites, clinic staff will consecutively approach and directly present the study to those 18 years and older or the adult caregiver for adolescents younger than 18. Both interested AYAHIV and caregivers will be referred to the study staff for recruitment. The study staff will give AYAHIV more details on the study procedures, screen AYAHIV for eligibility using criteria in Table 1, and finally obtain informed consent from AYAHIV 18 years and older or assent from adolescents aged 12–17 of consenting caregivers. Eligible adolescents aged 10–11 will be given information sheets that describe the study, and consent for their participation will be obtained from their caregivers. The study staff will note reasons for ineligibility and/or refusal and AYAHIV will be replaced until target sample is reached at each site.

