### Sample size and power

#### Primary outcome

The primary outcome analysis will compare AYAHIV virologic suppression at 12 months post-intervention, between intervention versus control sites using generalized estimating equations with robust standard errors, providing unbiased marginal estimates of the intervention effect while adjusting for within-cluster correlations.

For the primary outcome, sample size estimates are based on the following assumptions: 2-sided superiority test with 90% power at *α* = 0.05, clinic sizes of 220 AYAHIV in active care per clinic (range, 113–590), levels of viral suppression < 50 copies/mL of 65% in control clinics (current data estimates this proportion at 48–68%), *ICC* = 0.05 (range, 0.04–0.08). Thus, we estimate that 12 clusters sampling at least 100 AYAHIV each on average will provide > 80% power to detect an absolute increase of 16% in virologic suppression in the intervention versus control clinics.

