##### Retention

Projected statistical power for the comparison between arms for the secondary retention outcomes between intervention versus control sites assumes clinic “in care” population sizes of an average of 220 AYAHIV in active care (12-month period) for a total analysis size = 2640 across 12 sites and an assumed proportion retained in care (90-day window) of 50–60% under control conditions.

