## Trial status

The trial presented here is aligned with IRB protocol version 1.3, approved on 02 August 2021. The recruitment started on 13 September 2021 and is anticipated to be completed in December 2022.

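### The clinic size of 220 is used in three incompatible ways, and no sample from 1200 to 2400 gives the stated power above 80% at the plan's own 65% v 81% and ICC of 0.05

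*Protocol article*

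**What the plan says.** All places are in the protocol article.

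- **Participants and recruitment, Table 1:** the anticipated number of adolescents and young people is "a minimum of 1200 and a maximum of 2400 for the post-intervention assessment". The AYAHIV subsection words the upper figure as a cap: "Up to 2400 AYAHIV (maximum of 200 AYAHIV per site) will be recruited". Patients are approached at clinic visits, and those who are ineligible or refuse are replaced until the site's target is met.
- **Study setting:** a clinic was eligible only if it had 220 or more patients aged 10–24 active on ART.
- **Sample size and power, Primary outcome:** the inputs include "clinic sizes of 220 AYAHIV in active care per clinic (range, 113–590"), 65% suppression in control clinics, and an ICC of 0.05 with range 0.04–0.08. The paragraph opens with a "2-sided superiority test with 90% power at" α = 0.05 and ends by saying that "12 clusters sampling at least 100 AYAHIV each on average will provide > 80% power to detect an absolute increase of 16" percentage points.
- **Sample size and power, Retention:** the in-care population averages 220 per clinic, 2640 in total, with an "assumed proportion retained in care (90-day window) of 50–60% under control conditions".

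**The concern.** The three uses of 220 cannot all describe the same 12 clinics. If 220 is a floor, no clinic of 113 could have been selected. If it is both the floor and the average, every clinic has exactly 220 and there is no range. The number matters because the month-12 sample is drawn from people who attend, so clinic size and engagement together set how many can be recruited.

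The power sentence is the second issue. A reader will take 1200 as the size that secures more than 80% power, and will suppose that recruiting towards 2400 adds a comfortable margin. If neither holds at the plan's own inputs, a null result could be read as stronger evidence against the strategy than the design can supply.

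**Working it through.** **1. The plan's own totals reproduce.** 12 × 100 = 1200; 12 × 200 = 2400; 12 × 220 = 2640.

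**2. Engaged patients per clinic.** Formula: clinic size × proportion retained. Inputs: 220 and 50–60% (Retention); 113 and 590 (Primary outcome).

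| Clinic size | At 50% | At 60% | Share needed for 100 | Share needed for 200 |
|---|---|---|---|---|
| 113 | 57 | 68 | 177% to 147% | 354% to 295% |
| 220 | 110 | 132 | 91% to 76% | 182% to 152% |
| 590 | 295 | 354 | 34% to 28% | 68% to 56% |

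Over 12 clinics averaging 220, control-level retention gives 2640 × 0.50 = 1320 to 2640 × 0.60 = 1584. So 1200 fits and 2400 does not. Even if all six intervention clinics filled their cap of 200, the total would be 6 × 110 + 1200 = 1860 to 6 × 132 + 1200 = 1992.

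The documents give no participation rate. Assuming 70%, 80% and 90%, the 12 clinics yield 924–1109, 1056–1267 and 1188–1426.

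The 90-day figure is a rough proxy for who can be met. Trial status says "The recruitment started on 13 September 2021 and is anticipated to be completed in December 2022". If the 12 months of implementation began no earlier than that start date, month-12 recruitment lasts at most 109 days (13 September to 31 December 2022).

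**3. Power.** Inputs from Primary outcome: 65% v 65 + 16 = 81%, ICC 0.05, two-sided α = 0.05. Six clinics per arm follows from the 1:1 allocation of 12. Clinics are taken as equal in size, with m sampled in each.

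- Design effect = 1 + (m − 1) × ICC
- Effective n per arm = 6m / design effect
- SE = √[(0.65 × 0.35 + 0.81 × 0.19) / effective n] = √(0.3814 / effective n)
- Power ≈ Φ(0.16/SE − 1.96)

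At m = 100: design effect 5.95; effective n = 600/5.95 = 100.8; SE = 0.0615; 0.16/0.0615 = 2.60; power = Φ(0.64) = 73.9%.

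At m = 200: design effect 10.95; effective n = 1200/10.95 = 109.6; SE = 0.0590; 0.16/0.0590 = 2.71; power = Φ(0.75) = 77.4%.

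| ICC | m | Effective n per arm | Power, normal | Power, t with 10 df |
|---|---|---|---|---|
| 0.04 | 100 | 121.0 | 81.3% | 72.9% |
| 0.05 | 55 | 89.2 | 68.7% | 59.8% |
| 0.05 | 100 | 100.8 | 73.9% | 65.1% |
| 0.05 | 200 | 109.6 | 77.4% | 68.7% |
| 0.08 | 100 | 67.3 | 56.5% | 48.4% |
| 0.08 | 200 | 70.9 | 58.8% | 50.4% |

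The 10 degrees of freedom are 12 clinics minus 2. A pooled-variance version gives 72.9% at m = 100 and 76.4% at m = 200 for ICC 0.05.

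**4. Source of the gap.** As m grows, effective n per arm cannot exceed 6/0.05 = 120. Even unlimited sampling in 12 clinics would give only Φ(0.16/√(0.3814/120) − 1.96) = Φ(0.88), about 81%. Dropping from 100 to 55 per clinic (half of 110) costs 73.9 − 68.7 = 5.2 points. Moving the ICC from 0.04 to 0.05 at 100 per clinic costs 81.3 − 73.9 = 7.4 points with full recruitment.

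**The case against.** The strongest reply is that nothing here breaks the recruitment plan, and much of that stands.

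- **A reader might infer that the minimum does not fit.** It does: 1200 is below 1320–1584, and the plan asks for "12 clusters sampling at least 100 AYAHIV each on average", so large clinics can offset small ones.
- **A reader might treat 2400 as a failed target.** It is worded as a maximum, does not enter the power statement, and is a meaningful per-site cap for a clinic of 590.
- **The 110–132 is approximate.** Inclusion requires registration at the site, not a visit in the last 90 days, so new registrants and returning patients can add to it. If 220 really is a floor, the average is higher. Replacement of refusals is provided for, although it cannot enlarge the pool.
- **A reader might blame recruitment for the power shortfall.** The calculation does not support that. The shortfall is already present at the planned 100 per clinic.
- **A reader might suspect that the two-fold range lets an open-label team stop when results look favourable.** The documents contain no interim look or such rule. Randomization and blinding keeps everyone in data analysis, including the trial statistician, blinded until results are complete under dummy allocation. No inflation of type I error can be claimed.

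One could also say that the three 220s count slightly different things: active on ART, in active care, in active care over 12 months. The article does not say so, and gives no figures linking them.

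The power claim can be recovered under kinder inputs: ICC 0.04 (81.3% at 100 per clinic), or 68% control suppression with 200 per clinic at ICC 0.05 (80.6% unpooled, 79.6% pooled). Both use the favourable end of a stated range, not the assumption that the sentence names.

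**Conclusion.** The point holds in two parts.

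First, 220 is given as a floor, a value with range 113–590 and an average, and these need reconciling. On the average reading with 50–60% retained, 100 per control clinic is feasible but needs about 76–91% participation, and an average of 200 is out of reach. This rests on treating 90-day retention as a proxy for the people who can be met at month 12.

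Second, and more firmly, no size between 1200 and 2400 gives power above 80% at 65% v 81% and ICC 0.05. Power is about 74–77% by normal approximation, and about 65–69% with 10 degrees of freedom. The 90% named in the same paragraph is further away still. This assumes equal cluster sizes; unequal ones would generally lower power. The limit is set by the ICC and having only 12 clinics, and recruitment shortfall adds at most about 5 points under the 50% participation assumed here.

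The correction is worth making because it is specific and cheap. It does not show that the trial cannot recruit its minimum.

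**What to change.** 1. Take the actual counts at the 12 selected clinics and use them to reconcile Study setting, Primary outcome and Retention. Say whether 220 is a floor, a planning value or an average, which clinics the range 113–590 describes, and what is being counted in each place.
2. State the expected number per clinic at month 12 that follows from those counts and the retention assumption.
3. Justify the ceiling of 2400 or lower it to what the counts support.
4. Restate the power at the expected number and ICC 0.05, naming the method and whether it allows for 12 clusters, and replace the two power figures (90% and above 80%) with one.

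The cost is a wording change using counts that the sites should already hold. No extra enrolment is needed. The stated power becomes less favourable.
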